## Abstract

**Background:**

In adults with asthma, physical activity has been associated with several asthma outcomes. However, it is unclear whether changes in physical activity, measured via an accelerometer, have an effect on asthma control. The objective of the present study is, in adults with moderate-to-severe asthma, to investigate the effects of a behaviour change intervention, which aims to increase participation in physical activity, on asthma clinical control.

**Methods:**

This is a single-blind (outcome assessor), two-arm, randomised controlled trial (RCT). Fifty-five participants with moderate-to-severe asthma, receiving optimized pharmacological treatment, will be randomly assigned (computer-generated) into either a Control Group (CG) or an Intervention Group (IG). Both groups will receive usual care (pharmacological treatment) and similar educational programmes. In addition to these, participants in the IG will undergo the behaviour change intervention based on feedback, which aims to increase participation in physical activity. This intervention will be delivered over eight sessions as weekly one-on-one, face-to-face 40-min consultations. Both before and following the completion of the intervention period, data will be collected on asthma clinical control, levels of physical activity, health-related quality of life, asthma exacerbation and levels of anxiety and depression symptoms. Anthropometric measurements will also be collected. Information on comorbidities, lung function and the use of asthma medications will be extracted from the participant’s medical records.

**Discussion:**

If successful, this study will demonstrate that, in adults with asthma, a behavioural change intervention which aims to increase participation in physical activity also affects asthma control.

**Trial registration:**

Clinical Trials.gov PRS (Protocol registration and Results System): NCT-03705702 (04/10/2018).

## Background

Asthma is a chronic inflammatory airway disease that is defined by a variable expiratory airflow limitation and by respiratory symptoms such as wheezing, shortness of breath, chest tightness and cough [1]. People with asthma present paradoxical responses to physical activity. That is, although vigorous exertion induces exercise-induced bronchoconstriction (EIB), regular physical activity may be useful in the management of asthma [2]. Of note, the fear of becoming short of breath deters many people with asthma from taking part in regular activities and sports with their peers [2, 3].

In both health and disease, lower participation in physical activity has been associated with greater morbidity and mortality [4, 5]. In people with asthma specifically, lower levels of physical activity have been associated with an increased risk of disease exacerbation, increased frequency of medical visits and higher health care utilization [2, 4]. Therefore, the Global Initiative for Asthma (GINA) recommends that people with asthma engage in regular physical activity in order to improve their general health [1]. Several studies have reported the benefits of supervised exercise training on a broad range of outcomes in people with asthma such as disease exacerbation, clinical control, airway inflammation, psychosocial symptoms and exercise capacity [6–11]. These well-resourced studies may have limited application in regions that do not offer a program of supervised exercise training to people with asthma. Therefore, the current study plans to explore an alternative approach in which participants with asthma will engage in a behaviour change program which aims to increase participation in physical activity to produce health benefits and to improve asthma control.

Increasing participation in physical activity in daily life requires a conscious behaviour change [12]. According to some psychosocial models, behaviour change techniques that have shown promise build on participant confidence or self-efficacy to demonstrate the desired behaviour. Individual behaviour change techniques that have shown promise include; (i) education about why the change is worthwhile, (ii) action planning and, (iii) improving social support [13–15]. Therefore, behaviour interventions should include behaviour change techniques, such as self-monitoring, individual goal setting, feedback on behaviour, problem-solving coping planning and behaviour contract [16]. Others approaches (motivational interviewing) and considerations (managing relapses) are also important to overcome barriers and encourage adherence to the regimen [14, 17].

A significant number of studies have investigated the effects of behaviour interventions on physical activity in people with chronic obstructive pulmonary disease (COPD) [18]. However, to the best of our knowledge, only one study has investigated changes in physical activity in people with asthma [19]. At enrolment of that study, all patients were instructed in the benefits of physical activity, were given a pedometer, and made a contract to be more physically active. Patients in the intervention group also received instruction in linking positive affect and self-affirmation to physical activity. The authors concluded that a multiple-component protocol was effective at increasing physical activity in people with asthma, but an intervention to increase positive affect and self-affirmation was not effective within this protocol [19]. Despite the novelty of this study, we can consider it has two bias. First, it was conducted in people with mild to moderate asthma, who had minimal impairment in physical fitness and minimal number of comorbidities. Previous studies have demonstrated that patients with more severe asthma seem to obtain the greatest benefit from exercise training [8, 20, 21]. Second, physical activity was quantified by using a questionnaire that can present a recall bias [19]. In addition, the study did not assess sedentary behaviour (SB), which has been associated with negative health consequences [22].

In the past several years, sedentary behaviour (SB) has received considerable attention due its association with the increased risk for all-cause mortality in the general population [22]. SB is defined as any activities or behaviours (other than sleep) that are characterized by low energy expenditure (≤ 1.5 MET, metabolic equivalent of task), including activities such as sitting, reclining or being in a lying position [23]. Even patients with COPD who perform the recommended 150-min of MVPA per week spent most of their time engaged in sedentary behaviour or in light intensity PA [24]. In patients with asthma, a higher sedentary time has been associated with decreased exercise capacity and asthma control [25]; however, strategies to reduce the time in SB in this population remains largely unknown.

The main objective of the present study is, in adults with moderate-to-severe asthma, to investigate the effects of a behaviour change intervention, which aims to increase participation in physical activity, on asthma clinical control. Changes in sedentary behaviour, sleep, health-related quality of life and psychosocial symptoms will be also evaluated to better understand how physical activity might influence asthma control. Our hypothesis is that the behaviour intervention will be effective at increasing physical activity levels and improving clinical control in adults with asthma.

## Methods/design

### Participants

The study will include adults, aged 18 to 60 years, with moderate or severe persistent asthma [1], clinically stable disease (without hospitalizations, emergency care or medication changes for at least 30 days), who have been undergoing medical treatment for at least 6 months [8]. Patients will be required to report that they are not meeting the current guidelines for sufficient physical activity (i.e. performing < 150 min of moderate to vigorous physical activity per week) [26] and should have uncontrolled asthma according to the asthma control questionnaire (i.e. ACQ score > 1.5) [27]. The exclusion criteria will comprise the presence of any underlying lung condition other than asthma; significant cardiovascular or musculoskeletal disease that may compromise the participant’s capacity to participate in physical activity; active cancer; and uncontrolled hypertension or diabetes. People who are participating in other research studies, those who are unable to understand our questionnaire, as well as pregnant women, smokers or ex-smokers (≥ 10 pack-years), will also be excluded.

### Study setting

Participants will be recruited from an outpatient asthma clinic at a University Hospital in São Paulo. The Hospital Research Ethics Committee of the University of São Paulo has approved the study (66375617.1.0000.0068), and all of the patients will provide written informed consent before participating. This study has been registered on Clinical Trials.gov PRS (Protocol registration and Results System): NCT-03705702 (04/10/2018).

### Experimental design

This is a single-blind (outcome assessor), two-arm, randomised controlled trial (RCT). Adults with asthma will be invited to participate in the study after a regular medical visit, and asthma pharmacotherapy will be maintained during the intervention. All of the eligible participants will be randomly assigned to either a control group (CG) or an intervention group (IG). Both groups will receive usual care (pharmacological treatment) and similar educational programmes. In addition to these, participants in the IG will undergo the behaviour intervention based on feedback, which aims to increase participation in physical activity. Both before and following the completion of the intervention period, data will be collected on asthma clinical control, levels of physical activity, health-related quality of life, asthma exacerbation, levels of anxiety and depression symptoms. Anthropometric measurements will also be collected. Information on comorbidities, lung function and the use of asthma medications will be extracted from the participant’s medical records. The protocol foresees has 12 weeks including 8 weeks of intervention and 4 weeks of evaluation (2 weeks before and 2 after the intervention). The study flow diagram is presented in Fig. 1 and the study schedule in Table 1.

**Fig. 1 Fig1:**
[figure not shown]
Study flow diagram. Assessment will be performed during two visits. Eligible participants will be randomly assigned to either the Control Group (CG) or the Intervention Group (IG). Participants in both groups will receive the same educational program. In addition, participants in the IG will undergo the eight-week behaviour intervention aimed at increasing participation in physical activity. Re-assessment will occur following the completion of the intervention period

**Table 1 Tab1:** SPIRIT schedule of study recruitment, intervention and assessments. Group allocation will occur after a regular medical visit at the Pulmonary Division of the University of Sao Paulo Clinics Hospital; t1 = month 1; t2 = month 2; t3 = month 3

Timepoint	STUDY PERIOD				
	Enrolment	Allocation	Post-allocation		
	*-t* _*1*_	0	*t* _*1*_	*t* _*2*_	*t* _*3*_
Enrolment:					
Eligibility screen	X				
Informed consent	X				
Allocation		X			
Interventions:					
Educational programme		X	X		
Behaviour intervention		X	X	X	
Assessments:					
Anthropometric data, comorbidities, medication, onset of asthma, lung function	X				X
Asthma Clinical Control	X				X
Physical Activity levels	X	X	X	X	X
Health-related quality of life		X			X
Asthma exacerbation		X			X
Anxiety and Depression symptoms		X			X

### Randomisation and blinding

The randomisation sequence will be computer-generated and implemented by an investigator who is unaware of the sequence and is not involved in recruitment, assessment or treatment. The randomisation sequence will be concealed using opaque envelopes that are sequentially numbered as previously described [28]. Each envelope will correspond to one of the two study groups, and an envelope will be picked by the participant after the baseline assessments. The nature of the interventions will preclude the blinding of the participants and blinding of the physiotherapist who will deliver the education and behaviour intervention. However, the outcome and the statistic assessor will be blinded to group allocation.

### Interventions

#### Educational programme

Participants in both the CG and the IG will complete a similar educational programme consisting of two 90-min classes, held in different weeks. The classes will include an education videotape, presentations and group discussions. The first class will address asthma education, which will include information about the pathophysiology of asthma, instructions on both medication and use of the peak flow meter, self-monitoring techniques, environmental control techniques and avoidance strategies [1, 29]. The second class will address the current international physical activity recommendations as well as the importance and benefits of being physically active and maintaining a healthy lifestyle [26].

#### Behaviour intervention

Participants in the IG will undergo a behaviour counselling programme, combined with a monitoring-and-feedback tool, which will aim to increase participation in physical activity. The behaviour intervention will be based on the transtheoretical model, which recognizes behaviour change as a dynamic process that moves through stages and that reinforces change via goal-setting, skill-development and self-control [14, 30]. Participants will be requested to attend eight one-on-one face-to-face goal-setting consultations, once a week, with each consultation lasting approximately 40 min. At the beginning of the intervention, a motivational interview will be conducted, in order to identify the physical activity behaviour stage the participant is at, by using a validated questionnaire [31]. Participants will be offered a commercially available activity monitor (wearable device), known as a Fitbit Flex 2 (Fitbit Inc., San Francisco, CA, USA), to wear during the 3 days prior to each consultation. During each weekly consultation, data from the activity monitor will be downloaded and reviewed. An individual action plan, tailored according to each participant’s level of physical activity and behaviour change stage, will be established with realistic goals in order to increase the time spent in physical activity. After 3 weeks of intervention, discussion about sedentary behaviour will be implemented to raise awareness of the risks of prolonged uninterrupted periods of sitting in order to reduce time spent sedentary (i.e. sitting, reclining or lying during waking hours). Participants will be asked to complete a physical activity diary (daily book) and sign a contract with the health professional in order to commit to an action plan.

Weekly physical activity goals will be set using data provided by the “Fitbit”, using the behaviour change techniques such as self-monitoring, individual goal setting, feedback on behaviour, problem-solving coping planning, behaviour contract, as also others approach (motivational interviewing) and considerations (managing relapses) [13–16]. During the last eight consultation, participants will be interviewed in order to identify the any change in behaviour stage as well as to discuss the goals that have been achieved, the benefits of participating in the behaviour intervention, the strategies that were used to overcome barriers to physical activity and the long-term goals that will be used to remain physically active. The schedule and content of each individual session are summarized in Table 2.

**Table 2 Tab2:** Description of the behavioural change intervention sessions

No. Week	Topics covered
Week 1: Lifestyle choices	• Motivational interview to establish an educational diagnosis • Identify the behaviour stage regarding physical activity • Raise awareness of physical activity benefits • Provide the *Fitbit flex 2* and ask them to wear it for at least 3 days each week
Week 2: Why become physically active?	• Raise awareness of the physical activity international recommendations • Deepen the knowledge about the physical activity benefits for patients with asthma • Review *Fitbit flex 2* data of the past week and set one smart weekly goal (number of steps) • Establish the action planning (goal) and sign a contract • Evaluate the confidence of patients in achieving the goal (self-efficacy) • Explain about the use of the workbook, diary and vibration alert
Week 3: Sedentary behaviour	• Raise awareness of the risks of prolonged uninterrupted periods of sitting • Ask them to start monitoring their sitting time (diary in a workbook) • Discuss strategies to stand up/break up the sedentary time, according to the *Fitbit flex 2* vibration function • Review achievement (using the diary and *Fitbit flex 2* data) of the current goal • Discuss progress of the current goal • Set one smart weekly goal (number of steps)
Week 4: Dealing with barriers	• Dealing with barriers (as part of action and coping planning) • Brainstorm the main barriers and possible solutions/modifications • Discuss preferred activities • Invite participants to come up with ideas for walking (progression in duration/intensity) • Congratulate patients on any success (positive reinforcement) and ask them to reflect on any difficulties • Review achievement (using the diary and *Fitbit flex 2* data) of the current goal • Progress the current smart goal (number of steps and sedentary behaviour)
Week 5: Self-control	• Facilitate self-control (how to self-monitor the negative and positive behaviours regarding PA) • Identify the benefits acquired with the lifestyle change and reinforce the commitment to change • Invite participants to come up with ideas to break up the sedentary time • Review achievement (using the diary and *Fitbit flex 2* data) of the current goal • Progress current goal(s) as able/required
Week 6: Setting additional goal	• Review initial goal and discuss the progress of this goal (challenges) • Evaluate the confidence about achieving the new goal (self-efficacy) • Reinforce the health benefits of increased participation in PA and of breaking up sedentary time • Congratulate any success and reflect on any difficulties • Review achievement (using the diary and *Fitbit flex 2* data) of the current goal • Set a new smart goal as able/required
Week 7: Being rewarded	• Identify the behaviour stage regarding physical activity • Discuss the change (or not) that was achieved, as well as the benefits acquired with the new lifestyle • Discuss positive reinforcement • Review achievement (using the diary and *Fitbit flex 2* data) of the current goal • Set a final goal (number to steps)
Week 8: Goal balance	• Final motivational interview (goal setting, benefits acquired and strategies to overcome barriers) • Reinforce the importance of following through with these changes Establish a long-term goal to stay physically active

### Outcome measures

#### Primary outcome

##### Asthma clinical control

Asthma clinical control will be measured using the Asthma Control Questionnaire (ACQ). The ACQ, a reliable and validated tool [32, 33] that consists of five questions related to asthma symptoms (daytime and night-time symptoms, activity limitations, dyspnoea and wheezing), one question on rescue medication (the use of short-acting β_2_ agonists) and one question on lung function (forced expiratory volume in 1 s [FEV_1_] before bronchodilation expressed as a percent of the predicted value). The score of the ACQ ranges between 0 and 6. Scores lower than 0.75 are associated with good asthma control, whereas scores greater than 1.5 are indicative of poorly controlled asthma [27]. A change of at least 0.5 points in the ACQ score is regarded as being clinically significant [34].

#### Secondary outcomes

##### Levels of physical activity and sleep

Levels of physical activity and sleep will be objectively measured by an accelerometer (Actigraph GT9X, Actigraph, Pensacola, FL, USA) [35]. The device will be initialized via a computer interface in order to collect data in 60-s epochs on the 9 axes by using specific software (ActiLife 6.13.3 Firmware version). Each participant will be instructed to wear the device, on the waist (using an elastic belt) during the day and on the non-dominant wrist at night, for seven consecutive days both before and following the completion of the intervention period. Data will be presented as the average number of steps per day (steps/day), as well as the time spent in moderate to vigorous physical activities (MVPA, minutes/day) (≥ 1951 cpm), light-intensity physical activity (≥ 100 and < 1951 cpm) and time spent sedentary (< 100 cpm), expressed as the percentage of waking hours. The outcomes derived from the sleep monitor will be sleeping latency (the amount of time needed to fall asleep) and sleep efficiency (number of sleep minutes divided by the total number of minutes the participant was in bed). The device is a valid and reliable method for detecting sleep/wake diurnal patterns compared with polysomnography [36].

##### Asthma-related quality of life

Health-related asthma quality of life will be assessed by the Asthma Quality of Life Questionnaire (AQLQ). The AQLQ comprises four domains: activity limitations, symptoms, emotional function and environmental stimuli. The AQLQ has been translated into Portuguese and validated in a Portuguese-speaking population [37]. The AQLQ score ranges between 0 and 7 and the higher the score, the better the quality of life. An improvement of 0.5 points following intervention is considered to be clinically significant [38].

##### Asthma exacerbation

Asthma exacerbation is defined as the occurrence of events that are troublesome to the patient or that require urgent action on the part of the patient and physician, thus prompting a need for a change in treatment [39]. At least one of the following criteria will be used to define an exacerbation during the current study: the use of ≥4 puffs of rescue medication per 24 h during a 48-h period; a need for systemic corticosteroids; an unscheduled medical appointment and either a visit to an emergency room or a hospitalization [29, 39].

##### Anxiety and depression symptoms

Symptoms of anxiety and depression will be assessed by the Hospital Anxiety and Depression Scale (HADS) [40], which consists of 14 items divided into 2 subscales (7 for anxiety and 7 for depression). Each item is scored from 0 to 3, with a maximum score of 21 points for each subscale. The HADS uses a cut-off score to classify participants as having or not having symptoms of anxiety or depression (score > 9 each) [41].

##### Anthropometric indexes

Height, body-weight (Filizola®, Brazil), waist circumference, hip circumference and waist-to-hip ratio (WHR) will be measured by using a standardized protocol [42, 43]. Participants body mass index (BMI) will be obtained by dividing body-weight (in kilograms) by their height (in metres squared) [44].

### Data analysis

A sample of 46 participants has been estimated as the number needed to provide 80% power in order to detect a between-group difference (favouring the IG) of 0.5 ± 0.7 in the ACQ score (effect size of 0.7) [34]. The final sample size will be set at 55 patients, assuming up to a 20% loss during follow-up, as described previously [8, 29]. The results will be analysed according to the intention-to-treat principle, as recommended by the CONSORT statement [45], using specific software (SigmaStat 3.5, Systat Software Inc.). The distribution of the data for the continuous outcomes will be assessed using the Shapiro Wilk test. Data that are not normally distributed will be transformed, and a repeated measure ANOVA will be used to test the interactions between time and treatment. A Holm-Sidak correction will be applied in order to adjust for multiple comparisons. *P* values < 0.05 will be considered statistically significant.

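### On its own inputs (difference 0.5, SD 0.7, 5% level), the planned 46 participants give about 66% power, not 80%; 64 would be needed

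*Protocol article*

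**What the plan says.** The sample size is set out in the Data analysis section of the protocol article. The target is "a between-group difference (favouring the IG) of 0.5 ± 0.7 in the ACQ score", which the article summarises as an "effect size of 0.7". From this it concludes: "A sample of 46 participants has been estimated as the number needed to provide 80% power". It then allows for attrition: "The final sample size will be set at 55 patients, assuming up to a 20% loss during follow-up".

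The same section gives the test ("a repeated measure ANOVA will be used to test the interactions between time and treatment") and the significance level (P "values < 0.05 will be considered statistically significant"). The ACQ is the primary outcome, and the Primary outcome section takes a change of at least 0.5 points as clinically significant. The article states no sidedness, no allocation ratio and no correlation between baseline and follow-up. It does not say whether 0.7 is the SD of the ACQ score or of its change.

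**The concern.** All the quantities for a standard two-group calculation are given, and the quoted effect size is simply 0.5/0.7. Such a calculation needs just over 30 participants per arm, whereas 46 in total is 23 per arm.

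This is the power claim for the primary outcome, set at the article's own threshold for clinical significance. A reader will take a null result as coming from a trial with an 80% chance of detecting a 0.5-point benefit. If the real chance is nearer two in three, that result says much less about the absence of an effect.

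**Working it through.** **Inputs**

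- From the Data analysis section: difference 0.5, SD 0.7, power 80%, alpha 0.05, 46 evaluable, 55 randomised, 20% loss.
- Assumed: 1:1 allocation, which gives the highest power for a fixed total.
- Assumed: a two-sided test, because the F test of a time-by-treatment interaction is two-sided. With two arms and two time points, that interaction is equivalent to a two-sample t test on change scores.

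**Step 1. Effect size.** d = 0.5/0.7 = 0.714, which the article rounds to 0.7.

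**Step 2. Required sample size.** The normal approximation is n per arm = 2(z₀.₉₇₅ + z₀.₈₀)²/d².

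- d = 0.714: 2 × (1.960 + 0.842)²/0.714² = 30.8, so 31 per arm (62 in total).
- d = 0.70: 32.04, so 33 per arm (66 in total).

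The exact calculation uses the noncentral t distribution.

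- d = 0.714: 31 per arm gives 79.0% and 32 per arm gives 80.3%, so 64 in total.
- d = 0.70: 33 per arm gives 79.97%, so strictly 34 per arm (68 in total).

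None of these gives 46.

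**Step 3. Power at 46.** With 23 per arm the noncentrality is d√(n/2) = 0.714 × √11.5 = 2.42, and the critical t on 44 degrees of freedom is 2.015.

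- Noncentral t: 65.9% (64.1% at d = 0.70).
- Normal approximation: Φ(2.42 − 1.96) = 67.8% (66.1% at d = 0.70).

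**Step 4. Detectable difference.** 80% power with 23 per arm needs d = 0.845, so 0.845 × 0.7 = 0.59 points. Equivalently, detecting 0.5 points would need an SD of 0.5/0.845 = 0.59.

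**Step 5. Attempts to recover 46**

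| Reading | N needed | Power |
|---|---|---|
| One-sided 5%, d = 0.714 | 50 | 77.0% at 46 |
| One-sided 5%, d = 0.70 | 52 | 75.6% at 46 |
| 46 per arm | – | 92% |
| Paired design | 18 | – |
| All 55 retained (27/28), two-sided | 64 | 73.9% |
| 44 left after 20% loss (22/22), two-sided | 64 | 63.9% |

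The last row arises because 55 × 0.8 = 44, which is below 46. Keeping 46 after a 20% loss needs 46/0.8 = 57.5, so 58.

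**Step 6. Correlation between baseline and follow-up (r), if 0.7 is the SD of a single score.** The SD of change is 0.7√(2(1 − r)), and the baseline-adjusted (ANCOVA) residual SD is 0.7√(1 − r²). Power with 23 per arm, two-sided:

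| r (assumed) | Change score / interaction | ANCOVA |
|---|---|---|
| 0.4 | 58% | 73% |
| 0.5 | 66% | 78% |
| 0.6 | 75% | 84% |
| 0.7 | 86% | 91% |

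The planned interaction test reaches 80% at r of about 0.64. If 0.7 is already the SD of change, its power is 66%.

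**The case against.** The strongest defence is that the true power cannot be known from this article. If 0.7 is the SD of a single score, a correlation of about 0.64 would bring the planned interaction test to 80% with 46, and a correlation might be recorded in a fuller protocol that is not shown. This stands as a limit on the claim: 66% is the power implied by the stated inputs, not a measured property of the trial. It does not rescue 46, because no correlation is given and the quoted effect size is the unadjusted ratio 0.5/0.7.

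A second defence is that the target is worded in favour of the intervention, which suggests a one-sided calculation. That narrows the gap to four participants (50 against 46) and gives 77% power. But it still does not yield 46, no one-sided test is declared, and the planned F test is not one-sided.

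Third, the loss is a ceiling, so more than 46 may be evaluable. That is true, but with all 55 retained the two-sided power is 74%. The plan therefore spans about 64% to 74%.

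Finally, moving to ANCOVA is a design choice rather than a correction of the arithmetic, and over-reading of a null result is a risk rather than a certainty. Both points are fair. Neither affects the finding that 46 does not follow from its inputs.

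**Conclusion.** The concern holds. No reading of the stated inputs gives 46 for 80% power. With 1:1 allocation, a two-sided 5% test and 0.7 as the SD of the quantity compared between arms, the requirement is 64. The planned 46 falls short by 18 evaluable participants, and power is overstated by about 14 percentage points (66% against 80%). The chance of missing a true 0.5-point difference is about 34% instead of 20%. The direction of the error is the same for one-sided and two-sided tests, for d of 0.714 or 0.70, and for the t or normal calculation. Only an unstated correlation or a smaller SD would change it. Because this is the power statement for the primary outcome, it must be corrected.

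**What to change.** Rewrite the sample-size paragraph. State whether the test is two-sided, whether 0.7 is the SD of the ACQ score or of its change, and any correlation assumed. Then take one of two routes, neither of which needs more patients:

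- **Restate the power for the planned test.** For example: with 46 evaluable participants, power is 66% for a 0.5-point difference (SD 0.7, two-sided 5%), and the difference detectable with 80% power is 0.59 points. This wording is right if 0.7 is the SD of change, or the SD of a score with r = 0.5. Otherwise recompute it with the stated correlation.
- **Make a baseline-adjusted (ANCOVA) analysis primary and give its power.** If 0.7 is the SD of a score, 46 participants give 78% at r = 0.5, and about 73% to 84% for r between 0.4 and 0.6. The value of r should be justified.

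The article says recruitment has begun, so the correction should be made before the analysis. The cost is one rewritten paragraph and a less favourable power statement. The second route also changes the primary analysis, and that has to be fixed before unblinding.

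### The 55 participants do not absorb the stated 20% loss: they leave 44 evaluable against the required 46, a small shortfall

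*Protocol article*

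**What the plan says.** The sample size stands in two consecutive sentences under Data analysis in the protocol article. The first gives the number required before any loss: "A sample of 46 participants has been estimated as the number needed to provide 80% power", for a difference of 0.5 with a standard deviation of 0.7 on the Asthma Control Questionnaire (ACQ), described as an effect size of 0.7. The second gives the number to enrol: "The final sample size will be set at 55 patients, assuming up to a 20% loss during follow-up", with two citations for the loss assumption.

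The Abstract (Methods) repeats the enrolled number: "Fifty-five participants with moderate-to-severe asthma, receiving optimized pharmacological treatment, will be randomly assigned". No other section gives a different loss rate, a different enrolment figure or an inflation formula. The significance threshold is given as: P "values < 0.05 will be considered statistically significant". The number of sides for the sample size calculation and the allocation ratio are not stated.

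**The concern.** Loss to follow-up happens to people who have been enrolled, so a 20% allowance is naturally read as 20% of the 55. On that reading the plan says that 46 evaluable participants remain after the worst loss it foresees, and they do not.

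This sentence is the article's only statement of how much attrition the primary comparison can absorb. Anyone monitoring retention would treat 10 or 11 losses as within plan, when the tenth loss already takes the evaluable number below the protocol's own requirement.

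**Working it through.** **Inputs.** Required 46, enrolled 55, loss up to 20%, difference 0.5, standard deviation 0.7, alpha 0.05 (all from Data analysis). Assumed because not stated: 1:1 allocation, a simple two-sample t-test, and 0.7 as the standard deviation of whichever quantity is compared. Both one-sided and two-sided tests are shown. The loss arithmetic in steps 1 to 3 needs none of these assumptions.

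**1. Reproducing the 55.** Multiplying the required number by (1 + loss): 46 × 1.20 = 55.2, which rounds to 55.

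**2. What 55 leaves.** Enrolled × (1 − loss): 55 × 0.80 = 44. Shortfall: 46 − 44 = 2. Largest tolerable loss: 55 − 46 = 9, and 9/55 = 16.4%. A tenth loss is 10/55 = 18.2%, still inside the stated 20%, and leaves 45.

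**3. What a 20% loss needs.** Required / (1 − loss): 46 / 0.80 = 57.5, rounded up to 58, which is 3 more than 55. Check: 58 × 0.80 = 46.4. Counting whole people only, 57 would just suffice (11/57 = 19.3%, leaving 46). On either count 55 is too few.

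**4. What the shortfall costs in power.** With n per arm, the noncentrality is d × √(n/2) on 2n − 2 degrees of freedom. For d = 0.5/0.7 = 0.714:

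- n = 22 (total 44): 0.714 × √11 = 2.37 on 42 degrees of freedom
- n = 23 (total 46): 0.714 × √11.5 = 2.42 on 44 degrees of freedom

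| Effect size | Test | Power at 44 | Power at 46 | Difference |
|---|---|---|---|---|
| 0.714 | two-sided | 63.9% | 65.9% | 2.0 points |
| 0.714 | one-sided | 75.4% | 77.0% | 1.6 points (1.7 unrounded) |
| 0.7 | two-sided | 62.1% | 64.1% | 2.0 points |
| 0.7 | one-sided | 73.9% | 75.6% | 1.7 points |

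**5. Cross-check that takes the 46 at its word.** Suppose 46 did give 80% two-sided power by whatever method was used. By the normal approximation, 44 would then give Φ[(1.960 + 0.842) × √(44/46) − 1.960] = Φ(0.780), about 78%. The cost is again about 2 points.

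**The case against.** Four points can be made for the plan.

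*The 20% may be meant as a margin on the 46.* The nine extra participants are 9/46 = 19.6% of 46, so this is probably what was intended. The text, however, speaks of loss during follow-up, and nothing in it attaches the 20% to the 46. The sentence still needs correcting, as loose wording of a common shortcut. That 46 was multiplied by 1.2 remains an inference from the match. The article shows no formula, and the cited sources for the loss assumption are not available here.

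*Analysis is by intention to treat.* This does not close the gap. The plan itself enlarges the sample for loss, so it treats those lost as not contributing to the 46. The ACQ is compared before and after the intervention, and a participant who is lost has no later value.

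*The effect is trivial.* This largely stands: three enrolled, two evaluable and about 2 points of power. No outcome, eligibility rule or analysis changes.

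*The power figures depend on unstated choices.* This also stands. The number of sides, the allocation ratio and the meaning of the standard deviation are not given, and the planned test is a repeated-measures time-by-treatment interaction. The figures are therefore shown as a range and labelled as assumptions.

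A reader who sees 64% power at 44 might infer that the faulty loss allowance takes the trial from 80% to 64%. It does not. By the same calculation, power at the full 46 is already 65.9%. The other 14 or so points (80 − 65.9 = 14.1) arise because the 46 does not follow from its stated inputs under these assumptions, which is a separate matter.

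**Conclusion.** The statement is wrong as written, and the effect is small. Fifty-five enrolled with a 20% loss leaves 44 evaluable, two below the protocol's own requirement. The true tolerance is 9 losses, or 16.4%. This rests only on the three stated figures (46, 55 and 20%) and on reading the loss as a share of those enrolled.

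The cost in power, about 2 points, holds for one-sided and two-sided tests and for either effect size, given 1:1 allocation and a simple two-group comparison.

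It would go too far to conclude that enrolling 58 makes the trial adequately powered. Fifty-eight repairs the loss allowance only: after a 20% loss it brings back 46 evaluable, and 46 does not reach 80% on the stated inputs with either kind of test. The point merits a correction but is minor beside the derivation of the 46.

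**What to change.** Keep 55 and restate the sentence under Data analysis along these lines:

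> 55 participants keep 46 evaluable with up to 16% loss (9 participants); a 20% loss would leave 44.

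Add the power at 44 and at 46, and state the number of sides, the allocation ratio and what the standard deviation of 0.7 refers to.

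Re-derive the 46 first, because the tolerance depends on it: with N required, 55 absorbs a loss of 1 − N/55. For a simple t-test at 0.5/0.7 and 80% power, N is 50 one-sided, and 55 then absorbs 5 losses (5/55 = 9.1%). Two-sided, N is 64, and 55 falls below it before any loss. The revised wording should not present 46 evaluable, or 58 enrolled, as securing 80% power.

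If the sponsor prefers to keep the 20% allowance on a required 46, the enrolment figure is 58, and the Abstract must change with it.

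The cost is one corrected sentence and a less favourable stated tolerance. Recruitment had already begun (Trial status), and keeping 55 leaves enrolment, outcomes and analysis unchanged.
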